## Abstract

**Introduction:**

Undernutrition is an underlying cause of mortality in children under five (CU5) years of age. Animal-source foods have been shown to decrease malnutrition in CU5. Livestock are important reservoirs for *Campylobacter* bacteria, which are recognised as risk factors for child malnutrition. Increasing livestock production may be beneficial for improving nutrition of children but these benefits may be negated by increased exposure to *Campylobacter* and research is needed to evaluate the complex pathways of *Campylobacter* exposure and infection applicable to low-income and middle-income countries. We aim to identify reservoirs of infection with *Campylobacter* spp. of infants in rural Eastern Ethiopia and evaluate interactions with child health (environmental enteric dysfunction and stunting) in the context of their sociodemographic environment.

**Methods and analysis:**

This longitudinal study involves 115 infants who are followed from birth to 12 months of age and are selected randomly from 10 kebeles of Haramaya woreda, East Hararghe zone, Oromia region, Ethiopia. Questionnaire-based information is obtained on demographics, livelihoods, wealth, health, nutrition and women empowerment; animal ownership/management and diseases; and water, sanitation and hygiene. Faecal samples are collected from infants, mothers, siblings and livestock, drinking water and soil. These samples are analysed by a range of phenotypic and genotypic microbiological methods to characterise the genetic structure of the *Campylobacter* population in each of these reservoirs, which will support inference about the main sources of exposure for infants.

**Ethics and dissemination:**

Ethical approval was obtained from the University of Florida Internal Review Board (IRB201903141), the Haramaya University Institutional Health Research Ethics Committee (COHMS/1010/3796/20) and the Ethiopia National Research Ethics Review Committee (SM/14.1/1059/20). Written informed consent is obtained from all participating households. Research findings will be disseminated to stakeholders through conferences and peer-reviewed journals and through the Feed the Future Innovation Lab for Livestock Systems.

Strengths and limitations of this studyComprehensive characterisation of all *Campylobacter* spp. in a smallholder setting in Africa in humans, livestock and environment.First study with a specific focus on transmission of non-thermotolerant *Campylobacter* spp. from livestock reservoirs.Longitudinal design allows evaluation of infection and disease dynamics.Relatively small sample size, affecting power to detect nutritional impacts of *Campylobacter* colonisation in infants.Execution heavily affected by COVID-19 pandemic, civil conflict and other stressors.

In recent years, two randomised controlled trials found no significant effect of traditional WaSH interventions on stunting.^16^ Researchers subsequently called for ‘transformative WaSH’ to eradicate household faecal contamination. Without tackling environmental contamination (animal waste, soil, poor food hygiene), the negative findings on child growth persisted in a recent intervention implementing this transformative approach, despite finding a partial protective effect against EED.^17^ These findings emphasise the necessity of targeting exposure to animal faeces and zoonotic enteric pathogens through effective control measures in future interventions, particularly where livestock farming contributes significantly to rural livelihoods.

A recent risk-benefit analysis of smallholder livestock production summarised a variety of enteric pathogens originating from livestock and associated with EED and undernutrition. Mainly, asymptomatic infections of children with *Campylobacter* spp were found to be associated with EED outcomes of epithelial damage, inflammation and increased permeability of the gut, as well as growth faltering and reduced weight gain.^13^ A study in Peru found that asymptomatic infection of *Campylobacter* had a stronger effect size on slowing weight gain than its symptomatic counterpart.^18^ In the Etiology, Risk Factors, and Interactions of Enteric Infections and Malnutrition and the Consequences for Child Health (MAL-ED) study, *Campylobacter* spp in child stools detected by Enzyme-Linked Immuno Assay (ELISA, identifying all species in the genus) had a nearly twofold higher effect on growth faltering than the thermotolerant species *C. jejuni*/*C. coli* detected by molecular methods, underscoring the potentially important role of non-thermotolerant *Campylobacter* spp. in undernutrition.^12 19^
*C. jejuni*/*C. coli* are the most common causal agents of bacterial enteritis globally,^20^ and their animal reservoirs include livestock animals.^21^ The epidemiology and reservoirs of non-thermotolerant *Campylobacter* (eg, *C. fetus*, C. *hyointestinalis*, Candidatus *Campylobacter infans*) are less well understood.^22^

We conducted a cross-sectional study of smallholder farming households in Haramaya woreda (district) in rural eastern Ethiopia to measure the prevalence of *Campylobacter* spp., EED and undernutrition in children aged 10–16 months old and related risk factors.^23^ A combination of poor child diet, inadequate WaSH conditions and poor livestock waste management potentially accounted for a high prevalence of (predominantly asymptomatic) *Campylobacter* spp colonisation, EED and undernutrition. Although the study was powered for prevalence estimation, current breastfeeding status of the child and child consumption of ASF were both significantly associated with *Campylobacter* spp. colonisation, while access to improved drinking water was protective against EED. Notably, we found a diversity of *Campylobacter* spp. colonised the children’s gut, with non-thermotolerant species occurring more frequently and in higher abundance than thermotolerant species.^24^ Although previous studies investigated the health impact and reservoirs of non-thermotolerant species, none of them targeted low-income and middle-income country settings and CU5 as study population.^25–27^ The findings from our cross-sectional study underscore the need for attribution research examining various livestock species and other potential reservoirs for *Campylobacter* colonisation of infants. This paper presents a longitudinal study protocol and adaptations that have been implemented due to political unrest and the COVID-19 pandemic.

The objectives of the longitudinal study are:

To assess the prevalence, species composition, and genomic diversity of thermotolerant and non-thermotolerant *Campylobacter* spp. in infants, adults, livestock and other reservoirs in the Haramaya woreda.To determine the attribution of *Campylobacter* infections in infants to humans, livestock and other reservoirs (ie, drinking water, soil) based on the genetic population structure of *Campylobacter* spp. circulating in these reservoirs.To assess the associations among the presence of *Campylobacter* spp. and the nutritional status (i.e., stunting) of infants in relation to their socioeconomic environment.

## Methods and analysis

### Study setting

The study is conducted in the rural Haramaya woreda, East Hararghe zone, Oromia Region, Ethiopia (figure 1). Haramaya woreda, at an altitude of 1400–2340 m above sea level, has 36 rural kebeles (the smallest administrative unit in Ethiopia) and three urban kebeles. Khat, vegetables and fruits are important cash crops.

**Figure 1 F1:**
[figure not shown]
Geographic location of study area. Right panels from top to bottom: Ethiopia, East Hararghe zone, Oromiya region with Haramaya woreda indicated in purple. Left panel: Haramaya woreda with study sites indicated in purple. Haramaya University (HU) campus is indicated in orange. The urban centre of Harar borders the woreda to the East. AM, Amuma; AW, Adele Walta; BG, Biftu Geda; BK, Bachake; DA, Damota; GC, Gobe Challa; IO, Ifa Oromia; KR, Kuro; NG, Nageya; QD, Qerensa Dereba.

According to the 2016 Ethiopian Demographic and Health Survey, stunting in Haramaya is higher at 45.8% than the national average of 38%.^28^ Haramaya University (HU) has established a Health and Demographic Surveillance Site (HDSS) in 12 kebeles in the Haramaya woreda.^29^ Overall, 10 of these 12 kebeles (figure 1) will provide the source population for the study. Two kebeles were excluded because of small population size and proximity to the urban centre of Harar. The total population of the 10 kebeles is 92 900, with population numbers per kebele ranging between 4900 and 14 300 (table 1).

**Table 1 T1:** Population size and number of participating households in selected kebeles

Kebele	Population	Participants	Kebele	Population	Participants
Adele Walta (AW)	5100	11	Gobe Challa (GC)	14 300	12
Amuma (AM)	7400	12	Ifa Oromia (IO)	12 200	11
Bachake (BK)	4900	9	Kuro (KR)	11 700	12
Biftu Geda (BG)	11 700	12	Nageya (NG)	11 500	12
Damota (DA)	6600	12	Qerensa Dereba (QD)	7500	12

Source: Haramaya University Health and Demographic Surveillance Site (unpublished).

### Sample size and power

The study is powered for prevalence estimation. A sample of 100 infants or animals allows estimation of a 50% prevalence with precision 10% at 95% confidence, and a power of 80%. We allowed for 20% attrition and aimed to enrol a sample of 120 newborn infants.

Overall, 100 pure cultures of each thermotolerant and non-thermotolerant *Campylobacter* spp. per reservoir (infants, mothers, siblings, four livestock species (cattle, goat, sheep, chicken), water, soil) are analysed by whole-genome sequencing, 1400 in total. This power calculation is based on Smid *et al*,^30^ who showed that the precision of attribution is reduced if less than 100 isolates per animal reservoir are used.

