### Study population

A birth registry has been developed, which leverages the biannual update of the HDSS by cross-tabulation of expected birthdates in the selected kebeles based on the date of the mother’s last menstrual period and the estimated month of pregnancy at the time of the interview. Data on expected deliveries were updated every month, and one DHSS data collector was assigned per kebele to record actual births. Newborn children were randomly selected with the aim to include 12 infants per kebele in the first month after birth. Families were eligible for participation if they had no plans to move out of the Haramaya woreda within 6 months; the mother had resided in the woreda for at least 3 months during pregnancy; and the mother was over 16 years of age when giving birth. Infants were excluded if the birth weight was <2500 g, if the infant or mother required extended stay (more than 4 days) in the hospital after birth, or if the infant had visible congenital abnormality or known serious medical illness or enteropathy, diagnosed by a medical doctor. Enrolment started in December 2020 and was completed by June 2021; 115 infants have successfully been enrolled (table 1). Written informed consent was obtained from all participating households (husband and wife) using a form in the local language (Afan Oromo).

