### Data analysis

#### Objective 1

The prevalence, species composition and genomic diversity of thermotolerant and non-thermotolerant *Campylobacter* spp. in infants, adults, livestock and other reservoirs in the Haramaya woreda will be characterised by descriptive analysis; identification of species and clonal complexes using legacy, core genome and/or whole-genome MLST: phylogenetic analysis,^39^ determination of index of diversity, linkage equilibrium and rarefaction analysis.^40^ Further, the virulome and resistome of the *Campylobacter* isolates will be analysed using comprehensive virulence factors^41^ and antibiotic resistance gene databases.^42^ In addition, a functional profiling of the sequenced genome will be predicted.^43^ Specificity and sensitivity of qPCR and culture methods for detecting *Campylobacter* at the genus and biological group levels will be evaluated using Bayesian modelling of performance characteristics in the absence of a gold standard.^44–46^ Metagenomic sequencing data will be analysed by analysed by latest versions of QIIME V.2,^47^ CCMetagen^48^ and IDseq pipelines.^49^

We will fit a Bayesian two-state Markov model for the temporal process of colonisation and clearance of *Campylobacter* in each infant. The daily transition probabilities between colonisation and clearance will be regressed on time, demographic variables, household characteristics and most recent *Campylobacter* prevalence among samples from livestock, environment and other household members (sampled biannually).

Spatiotemporal effects will be analysed using boosted regression trees^50^ to model the influence of regional environmental variables on the distribution of infections of infants with the *Campylobacter* genus as primary outcome variable. Depending on results, this analysis will also be performed for one or more dominant species. To explore the spatial heterogeneity of effects of covariates on *Campylobacter* infections geographically weighted logistic regression models^51^ will be used.

#### Objective 2

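### The 80% power attached to the n = 100 prevalence calculation does not follow from it: the calculation supports only a precision statement, under simple random sampling, and the sample represents ten kebeles rather than the woreda

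*Protocol article*

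**What the plan says.** The section Sample size and power opens with "The study is powered for prevalence estimation" and then gives the basis: "A sample of 100 infants or animals allows estimation of a 50% prevalence with precision 10% at 95% confidence, and a power of 80"%. It names no null value, alternative or comparison to which the 80% could refer, and it states no sampling assumption.

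Under Study population: "Newborn children were randomly selected with the aim to include 12 infants per kebele in the first month after birth". Table 1 lists ten kebeles with 4900 to 14 300 residents (92 900 in total) and 9 to 12 participants each (115 in total).

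In the data analysis for Objective 1, prevalence and the related features, for infants and the other reservoirs of the Haramaya woreda, "will be characterised by descriptive analysis". Study setting says that the woreda has 36 rural and three urban kebeles. The source population is ten of the twelve kebeles in the university's surveillance site; the other two were left out for size and for closeness to Harar.

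**The concern.** A precision target and a power are answers to different questions. A half-width at a given confidence level describes an interval. Power describes a test of one stated value against another. The sentence gives both as results of n = 100, but its inputs (50%, 10 points, 95%) are those of an interval only.

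Prevalence is the one quantity for which the article gives a numerical precision and power, and its Discussion relies on that sizing when it explains what the study can and cannot detect. A reader could take the sentence to mean that a 10-point difference in prevalence would be found with 80% probability. The stated 10 points also rest on simple random sampling, which the allocation per kebele is not. And the result is described as belonging to a woreda of which only ten kebeles are observed.

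**Working it through.** **Inputs.** From Sample size and power: p = 0.50, d = 0.10, 95% confidence, n = 100. From Table 1: residents and participants per kebele.

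**1. The plan's own figure.**
- n = z² p(1−p)/d² = 1.96² × 0.25/0.10² = 96.04, so 97 after rounding up.
- Half-width at n = 100: 1.96 × √(0.25/100) = 0.098, or 9.8 points.

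So n = 100 and 10 points reproduce under simple random sampling. No power enters the formula.

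**2. Power, if a test is supposed.** The documents name no test. The nearest reading is a two-sided 5% one-sample test of 50% when the truth is 60% (or 40%).
- Standard errors: √(0.25/100) = 0.0500 under the null and √(0.24/100) = 0.0490 under the alternative.
- Power = Φ[(0.10 − 1.96 × 0.0500)/0.0490] = Φ(0.041) = 0.516.
- Exact binomial: rejecting at 61 or more has an upper tail of 0.018 and power 0.462. A cut-off of 60 has an upper tail of 0.028, above 0.025, and power 0.543.
- n for 80% power: [(1.96 × 0.5 + 0.842 × √0.24)/0.10]² = 193.8, or 194.
- Difference with 80% power at n = 100: (1.96 + 0.842) × 0.05 = 0.140, or 14 points.

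**3. Other readings tried for the 80%.**

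| Reading | Result |
|---|---|
| One-sided 5% test, 10 points | 64–65% |
| Two groups of 100, 50% against 60% | 29% |
| Two groups of 50, 50% against 60% | 17% |
| Chance that the half-width is at most 10 points, Wald or Wilson interval | 100% |
| The same, Clopper–Pearson interval | 6% |

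None gives 80%.

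**4. Allocation across the ten kebeles.** Let w_k = residents/participants in kebele k. This stands in for the true sampling weight only if eligible births are proportional to residents.
- Participants per 1000 residents run from 12/14.3 = 0.84 to 11/5.1 = 2.16.
- Kish factor = n Σ n_k w_k²/(Σ n_k w_k)². Here Σ n_k w_k = 92 900 and Σ n_k w_k² = Σ residents²/participants ≈ 82.32 million, so the factor is 115 × 82.32 million/92 900² = 1.097.
- Weighted half-width at n = 100: 9.8 × √1.097 = 10.3 points.
- At n = 115, with every enrolled infant contributing: 1.96 × √(0.25/115) × √1.097 = 9.6 points.

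**The case against.** The best defence is that the study estimates and does not test. Any n chosen to give a 95% half-width of d has about 50% power against a shift of d, by construction. The 52% is therefore not a shortfall peculiar to this study, and the operative figures (n = 100, about 10 points) are sound under simple random sampling. All of that stands. A reader might infer that the study is undersized for its purpose, and the documents do not support that. The fault is a power claim that belongs to no stated hypothesis.

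Three further inferences are tempting and go too far:
- *That prevalence will be analysed unweighted and without regard to kebele.* Calling the analysis descriptive does not say so, and such detail may sit in a full protocol or analysis plan that is not shown. The article does plan spatial models under Objective 1 and adjusts for kebele residence under Objective 3.
- *That sampling fractions are known to differ 2.6-fold* (2.16/0.84). Table 1 counts residents, whereas newborns were sampled, and eligible births per kebele are not given.
- *That clustering widens the interval well beyond 10 points.* With 10 infants per kebele, an assumed intracluster correlation of 0.02 to 0.05 would give 9.8 × √1.18 = 10.6 to 9.8 × √1.45 = 11.8 points. The documents give no such correlation. For the ten kebeles, all of them sampled, kebele is a stratum and this inflation does not apply. For the whole woreda, a cluster variance would not rescue the claim either, because no random draw of the ten kebeles is described.

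**Conclusion.** The statement of 80% power is wrong as written. It does not follow from the stated inputs, and no standard reading tried recovers it. For a 10-point departure from 50%, tested two-sided at 5%, power at n = 100 is about 52% (46% exact); about 80% power goes with a 14-point difference. The 10-point test is a reading imposed here for scale.

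The precision figure is correct under simple random sampling, but that condition is not stated. Allowing for the near-equal allocation moves it only from 9.8 to about 10.3 points at n = 100, and 9.6 points at n = 115 stays within the stated 10. Both weighted figures assume that eligible births are proportional to residents.

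The sample can represent the ten surveillance kebeles. The documents give no basis for extending a design-based prevalence estimate to the whole woreda.

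**What to change.** 1. In Sample size and power, delete the words "and a power of 80"%. Alternatively, replace them with a statement of about 80% power to detect a 14-point difference from 50% (two-sided 5% test, n = 100).
2. In the same place, say that the 10-point precision assumes simple random sampling.
3. Secondary: for Objective 1, report infant prevalence weighted to the kebele populations with kebele as stratum, using Table 1 or, better, eligible births from the study's birth registry.
4. Describe the target of the prevalence estimate as the ten surveillance kebeles rather than the woreda.

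The first, second and fourth are changes of wording. The third uses figures already held and widens the intervals slightly, by a factor of about √1.097 = 1.05 under the births assumption. Enrolment is complete at 115, and none of these changes calls for more infants.

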### Collection and management of biological samples

Stool samples are obtained every 4 weeks from all infants and biannually from all mothers, siblings and livestock (one sample from chickens, cattle, goats and sheep per household). Samples from the environment (three soil samples using bootsocks and one sample of drinking water per household) are also collected biannually.

Mothers are provided modified disposable diapers with a clean plastic sheet, sterilised by UV for 10 min and an ice box with ice pack on the day before sample collection. The mother is asked to fit the modified diaper to the infant in the early morning and, after the infant has defecated, to wrap and place the diaper and contents in the ice box. When appropriate, the mother collects a sample of stool from the youngest sibling, as above, and of her own stool in a screw cap bottle. Stool samples are transferred to sterile prelabelled whirl-pack bags, which are transported to the lab in ice boxes.

Samples are transported to a dedicated laboratory at the HU main campus (figure 1) in an ice box within a maximum of 6 hours. Samples for nucleic acid extraction and sequencing are transferred to a nucleic acid stabilising reagent. On arrival in the laboratory, remaining faecal samples are distributed over barcoded tubes and frozen at – 80°C, partly with addition of 15% v/v glycerol. Samples for MPO analysis are distributed in barcoded tubes in the field, immediately flash-frozen in liquid nitrogen and stored at – 80°C immediately on arrival in the laboratory.

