Our study has several limitations. The study has been powered for prevalence estimation and source attribution of *Campylobacter* infections in infants, with a minimum target sample size of 100. This sample size is small to detect associations between nutritional outcomes and putative causal factors such as *Campylobacter* infection. For example, the MAL-ED study enrolled 165–237 infants per study site.^12^ Our sample size will allow us to detect relatively strong associations only. However, the MAL-ED study also demonstrated that the effect of the broad group of non-thermotolerant *Campylobacter* sp on linear growth is stronger than the effect of the well-known thermotolerant species *C. jejuni*. Our ability to detect several non-thermotolerant species separately by qPCR rather than at the group level by an all-inclusive immunoassay allows us to zoom in on the likely small number of species whose effect sizes may be larger than that of the whole group. The study is executed in unprecedented times of a major global pandemic and a major civil conflict in Ethiopia, leading to civic unrest, inflation and increased population mobility. This affects the ability to collect all samples and surveys as planned, resulting in an increased level of missing data. We are implementing several approaches to prevent missingness, including active communication with the CAB members, repeat visits and increasing the number of field workers to accomodate the additional workload and driving times. We will use multiple imputation methods to replace the missing data.

Awareness on the association between infant’s exposure to zoonotic pathogens in livestock faeces and risk of stunting is generally low, constraining initiatives to decrease exposure to these hazards. We aim to create an enabling policy and institutional environment, ensuring that smallholder livestock production and associated risk of EED receive the attention and investment this problem deserves. For example, farmers are unaware of the danger of livestock excreta or the measures they could take to reduce contamination. Health practitioners are unlikely to be equipped to diagnose and treat *Campylobacter* infections, especially those due to long‐term exposure to livestock. Due to lack of awareness, policy-makers and development partners may not prioritise reducing exposure to livestock faeces, in comparison to other food safety, WaSH and broader food security issues. Key strategies for this include the following:

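### The 20% attrition allowance does not protect the stated minimum of 100 infants: 125 would be needed, 120 leaves 96, and the 115 enrolled leave 92

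*Protocol article*

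**What the plan says.** Under Sample size and power, the protocol article bases the study size on prevalence. A sample of 100 is said to allow "estimation of a 50% prevalence with precision 10% at 95% confidence". The next step is the allowance for loss: "We allowed for 20% attrition and aimed to enrol a sample of 120 newborn infants".

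Under Study population, enrolment is reported as complete by June 2021: "115 infants have successfully been enrolled". The Discussion, written after enrolment had closed, describes the study as powered for prevalence estimation and source attribution, "with a minimum target sample size of 100".

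**The concern.** The three figures 100, 20% and 120 do not fit together. An allowance for loss should ensure that the required number is still there once the loss has happened, so the required number is divided by the fraction retained. The stated 120 is what results from adding 20% to 100 instead, and that leaves fewer than 100 at the end. Enrolment then stopped five short of 120, which widens the gap, yet the Discussion keeps 100 as the minimum without comment.

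At stake is whether the only justification given for the number of infants is true on the plan's own assumptions. A reader who takes 100 as a floor will expect a slightly better precision than the enrolled sample gives at the planned loss.

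**Working it through.** **Inputs**
- Required size 100; prevalence 50%, half-width 10 points, 95% confidence (Sample size and power).
- Attrition 20%; enrolment target 120 (Sample size and power).
- 100 described as a minimum (Discussion).
- 115 enrolled (Study population). The participants in Table 1 give the same total: 11 + 12 + 9 + 12 + 12 + 12 + 11 + 12 + 12 + 12 = 115.

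**Step 1. Reproduce the base size.** n = z² p(1 − p) / d² = 1.96² × 0.25 / 0.10² = 96.04, rounded up to 97. The stated 100 agrees with this as a rounded figure.

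**Step 2. Reproduce the enrolment target.**
- Dividing by the fraction retained: 100 / (1 − 0.20) = 125.
- Adding 20%: 100 × 1.20 = 120.

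From the stated 100, only the second calculation returns 120. From the unrounded formula value, 96.04 / 0.80 = 120.05, which is close to 120 but starts from a size the article does not state.

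**Step 3. Infants left after a 20% loss, and the precision they give.** Half-width = 1.96 × √(0.25 / n).

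| Enrolled | Left after 20% loss | 95% half-width at 50% prevalence |
|---|---|---|
| 125 | 100 | 9.8 points |
| 120 | 96 | 10.0 points |
| 115 | 92 | 10.2 points |

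**Step 4. Largest loss that still leaves 100.**
- From 120: 1 − 100/120 = 16.7%.
- From 115: 1 − 100/115 = 13.0%, that is 15 infants. A 20% loss from 115 is 23 infants.

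**The case against.** The best defence is that the real criterion is the 10-point precision, which needs only 96.04 infants, and 96.04 / 0.80 is 120.05. On that reading 120 is right and 100 is merely a rounded base. The article shows no derivation of 120, which is also simply 12 infants in each of 10 kebeles, so the claim that it was obtained as 100 × 1.20 is an inference. This stands in part: 120 enrolled with a 20% loss does meet the stated precision. It does not reconcile the text, because the article gives 100 in two places and calls it a minimum in one of them. Nor does it cover the sample actually enrolled, since 92 is below 96 as well as below 100.

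It is also fair to say that the 20% is an allowance and not an observation, that follow-up was later cut from 18 to 12 months, which may reduce loss, and that infants give stool every 4 weeks, so those who leave early still contribute data. The article openly acknowledges a small sample and increased missing data. All of this limits the consequence. None of it makes the stated numbers agree, and no revised attrition rate is given.

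A reader might go further and infer that 100 animals of each livestock species is also out of reach, because sampling is limited to "one sample from chickens, cattle, goats and sheep per household". The documents do not support that. For prevalence they set no 100 per species or per sampling round. The attrition allowance is given for newborn infants only. Livestock are sampled biannually, so one round is not the whole yield: if that means two rounds in 12 months (an assumption), the ceiling per species is between 2 × 92 = 184 and 2 × 115 = 230 samples if every household owns that species. No ownership figures are given, so no shortfall can be calculated. The 100 per reservoir in the same section refers to cultures for sequencing, which is a different quantity.

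**Conclusion.** The point holds for infants. On the article's own figures, an enrolment of 120 does not secure 100 infants after a 20% loss, and the 115 enrolled fall further short, at 92. The minimum of 100 is met from 115 only if attrition is at most 13.0%.

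The size is modest. The worst case at the planned loss is a half-width of 10.2 points against a stated 10, or 9.8 with 100 infants, and no analysis depends on that difference. It would be wrong to conclude that the study has already missed its minimum, since observed attrition is not reported.

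The result assumes that the planned 20% loss occurs, that the prevalence is 50%, and that precision is computed for one observation per retained infant with the simple binomial formula that reproduces the plan's base size.

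**What to change.** Under Sample size and power, keep the original target as history and add that 115 infants were enrolled, that 20% attrition would leave about 92 with a precision of about 10.2 points at 50% prevalence, and that 100 would remain only if attrition is at most 13%. In the Discussion, replace the minimum of 100 with the same statement, or describe 100 as the design figure and not as a floor.

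The cost is wording only. The stated precision becomes slightly less favourable, and no further enrolment or change to the analysis is needed.

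### The stated total of 1400 sequenced cultures does not match the plan's own inputs: nine listed reservoirs, two groups and 100 cultures of each make 1800

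*Protocol article*

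**What the plan says.** The second paragraph of the Sample size and power section in the protocol article gives a per-cell number, a list of reservoirs and a total. The per-cell number is "100 pure cultures of each thermotolerant and non-thermotolerant" Campylobacter. The list and the total follow: "per reservoir (infants, mothers, siblings, four livestock species (cattle, goat, sheep, chicken), water, soil) are analysed by whole-genome sequencing, 1400 in total". The number 100 is justified by a cited study, of which the article says that "the precision of attribution is reduced if less than 100 isolates per animal reservoir are used".

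The rest of the article keeps all these reservoirs in use. The objectives at the end of the Introduction attribute infant infections to "humans, livestock and other reservoirs (ie, drinking water, soil"). The section on collection of biological samples lists chickens, cattle, goats, sheep, soil and drinking water as separate items. The Objective 2 analysis takes as its primary outcome the share of infant infections attributed to mothers, siblings, livestock and the environment. The Discussion says that the study is powered for source attribution as well as for prevalence.

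**The concern.** The per-cell number, the reservoir list and the total stand in one sentence and cannot all be true. This sentence is the only sizing of the sequencing work behind source attribution, which is the subject of Objective 2.

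The possible explanations lead to different analyses:

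- If the total is a slip, nothing changes but a number.
- If some reservoirs or groups are not sequenced, attribution based on whole-genome data has no isolates for them.
- If reservoirs are pooled, the source categories that the study can report are coarser than those listed.

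A reader cannot tell which applies. If the choice is made once isolate yields are known, the source categories could follow the data.

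**Working it through.** **Inputs, all from the Sample size and power section**

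- Cultures per group per reservoir: 100.
- Groups: 2 (thermotolerant, non-thermotolerant).
- Reservoirs listed: infants, mothers, siblings, cattle, goat, sheep, chicken, water, soil, so 9.
- Stated total: 1400.

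**Attempt to reproduce the stated total**

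Total = reservoirs × groups × cultures = 9 × 2 × 100 = 1800. The stated 1400 is not reproduced.

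- Shortfall: 1800 less 1400 is 400.
- Relative shortfall: 400 divided by 1800 = 22%.
- Full reservoirs that 1400 covers: 1400 divided by (2 × 100) = 7.
- Cells that 1400 covers at 100 each: 1400 divided by 100 = 14, of 9 × 2 = 18.

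**Other ways to count**

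| Reading | Calculation | Total |
|---|---|---|
| Infants left out, as recipients | 8 × 2 × 100 | 1600 |
| Water and soil pooled | 8 × 2 × 100 | 1600 |
| Four livestock species as one | 6 × 2 × 100 | 1200 |
| One group only | 9 × 1 × 100 | 900 |
| Water and soil dropped | 7 × 2 × 100 | 1400 |
| Infants, mothers and siblings pooled | 7 × 2 × 100 | 1400 |
| Goats with sheep, and water with soil, pooled | 7 × 2 × 100 | 1400 |
| Five reservoirs with both groups, four with one | 5 × 200 plus 4 × 100 | 1400 |

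The last four readings reach 1400, but the article states none of them. Two also fit badly with its text. Dropping water and soil removes reservoirs that the attribution objective names. Pooling the three human groups mixes the recipients with two of their candidate sources.

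**What 1400 would mean under an even spread (illustration only)**

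- Per reservoir-by-group cell: 1400 divided by 18 = 77.8, about 78.
- Per reservoir, both groups combined: 1400 divided by 9 = 155.6, about 156.

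The first figure is below the plan's target of 100 of each group per reservoir. The second is above 100.

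**The case against.** The mismatch itself is hard to dispute. The case on the other side concerns what follows from it, and most of that case stands.

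**A reader might infer that each cell will hold only about 78 isolates.** The article does not support this. It nowhere spreads 1400 evenly, and 100 in each of 14 cells gives the same total. The total may also be a slip, with the target of 100 intact. Nor does the article call 1400 a cap or a budget, and the number of isolates obtained will also depend on culture yield.

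**A reader might infer that the plan breaches the threshold it cites.** This does not follow either. The threshold is worded per animal reservoir, not per reservoir and group. Even under the even spread, a reservoir would have about 156 isolates with both groups combined. The four livestock species at full target need 4 × 2 × 100 = 800, well within 1400. A figure of 78 would miss the cited threshold only if that threshold is applied to each group separately, which the article does not say. What it would miss is the plan's own target.

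**A reader might speak of nine sources.** Infants are the recipients in Objective 2, so the list holds at most eight candidate sources.

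It can also be said that the Objective 2 analysis does not refer to 1400, so no model or estimand depends on it. That is true and limits the harm. It does not remove the contradiction in the sentence that sizes the sequencing work.

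**Conclusion.** The stated total is wrong for the stated inputs. Nine listed reservoirs, two groups and 100 cultures of each give 1800; the article gives 1400, which is 400 or 22% too few. This rests only on counting the list and multiplying, and no other section of the article pools or drops a reservoir or group for sequencing.

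The consequence is conditional. If 1400 is the number to be sequenced, the target of 100 of each group cannot be met in all nine reservoirs. How the shortfall would fall on the reservoirs is not stated. The document also does not show whether the total, the list or the per-group target is the figure in error.

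The sentence should be corrected, because it is the stated sample size behind an objective for which the study is said to be powered, and the correction is cheap.

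**What to change.** Reconcile the three figures in the Sample size and power section, in one of these ways:

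1. **Restate the total as 1800.** As text this costs one number. If 1400 was the real plan, it also means 400 more cultures to obtain and sequence.
2. **Keep 1400 and say how it is made up.** State which reservoirs or groups are sequenced at 100 each, or which reservoirs are pooled. Carry the same source grouping into the Objective 2 attribution models, with infants as recipients and not as a source. For example, pooling goats with sheep and water with soil leaves mothers, siblings, cattle, small ruminants, chickens and environment: six sources, plus infants. That is 7 × 2 × 100 = 1400. It needs no extra sequencing, but the source categories are coarser and goats and sheep could no longer be told apart.
3. **If neither is done, restate the per-group target that 1400 can deliver.** Under an even spread over all 18 cells this is about 78.

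The change to the document is one sentence, plus a stated source grouping under the second option. The grouping should be fixed before isolate yields by reservoir are used to choose it.
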